### Methods in analysis to handle protocol non-adherence and any statistical methods to handle missing data {20c}

Compliance to the standard CLI or TIMED CLI will be tested based on the percentage of completion of modules on the MiGuide platform and attendance to the group meetings. Both completion of ≥ 80% of the modules, as well as ≥ 80% of the sessions, will be defined as compliant [94]. Both intention-to-treat and per-protocol analyses will be performed based on this compliance to the CLI. Additionally, adherence to the timed lifestyle behaviours will be self-reported and based on the timing of eating questionnaire, sleep questionnaire, and timing of physical activity questionnaire. These questionnaires will provide insight in adherence to the timed recommendations for all participants, both at baseline as well as changes during the follow-up period. To assess adherence, several sensitivity analyses will be conducted, comparing the timing of a certain lifestyle behaviour between baseline and follow-up. For example, participants who are already engaging in physical activity predominantly in the afternoon or evening, or those who transition towards physical activity in the afternoon or evening over the course of the study, will be considered adherent to the physical activity timing recommendations. This approach enables us to capture partial adherence to the different behaviours.

Fidelity of the coaches is assessed by checking the presentations that were given by the coaches during the session, which are uploaded to the MiGuide platform for the participants. When sessions are cancelled (due to unforeseen circumstances) and not rescheduled, this will be noted in a deviation form protocol by the researchers. Contamination of the timed advices between the TIMED CLI and standard CLI will be assessed by comparing the compliance results and adherence results. Furthermore, mixed model analysis will be used, which is able to account for missingness. We will therefore not do any imputation for missing data. Imbalances in participants’ characteristics between groups will not be tested statistically. However, clinically relevant imbalances will be addressed through sensitivity analyses that adjust for these variables.

### Plans to give access to the full protocol, participant level-data and statistical code {31c}

After finalization and publication of the study, access to the protocol and statistical code can be requested.

## Oversight and monitoring

### Composition of the coordinating centre and trial steering committee {5d}

[name] is the primary investigator of this study and responsible for ethical approval, coordination, and execution of the trial. [name] is the coordinating researcher, who is responsible for data collection and data management. As this is a pragmatic trial, there is no trial steering committee in place.

### Composition of the data monitoring committee, its role and reporting structure {21a}

There is no data safety monitoring board or safety committee established for this study given its low-risk profile.

### Adverse event reporting and harms {22}

To reduce the chance of adverse events (i.e. risk of hypoglycaemia), people taking sulfonylurea medication will be excluded from participation. Second, possible adverse events will be explained in the first group session and participants are advised to discuss possible events with their lifestyle coach and general practitioner. Given the non-invasive nature of the study procedures and intervention, no serious adverse events are anticipated. Any events that are spontaneously reported by participants or observed by the investigator and that have a sustained effect on the physical wellbeing of the participant will be documented and reported.

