### Eligibility criteria {10}

Eligible study participants are adults with an indication to be referred to a CLI by their general practitioner (Table 1). In addition, participants are excluded if they (1) are unable to provide written informed consent; (2) have serious mental impairment which would prevent them from understanding the study aim; (3) are pregnant; (4) work night shifts; and/or (5) take sulfonylurea medication. The latter is excluded, as the effects of reducing the eating window (part of the TIMED CLI) on the risk of hypoglycaemia in participants taking sulfonylurea medication is not sufficiently known.

**Table 1 Tab1:** Eligibility criteria for inclusion in the pragmatic trial: Indication for referral to a CLI

• Aged 18 years or older • Either (1) obesity (BMI ≥ 30 kg/m^2^); or (2) overweight (BMI ≥ 25 and < 30 kg/m^2^) with at least one comorbid condition: ◦ Sleep apnoea ◦ Vascular diseases ◦ Type 2 diabetes ◦ Osteoarthritis ◦ Increased waist circumference (men ≥ 102 cm; women ≥ 88 cm) • Motivated to change lifestyle behaviour • Digitally skilled and in the possession of a smartphone • Being able to speak and understand the Dutch language	

*CLI *Combined Lifestyle Intervention, *BMI *body mass index

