### Relevant concomitant care permitted or prohibited during the trial {11d}

There are no restrictions regarding concomitant care and medication use during this study.

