### Secondary outcomes

#### Fasting blood glucose and HbA1c

Participants receive the Contour Plus Blue glucose monitor, including test strips, lancing devices, and an information sheet. Using the device, they measure their blood glucose in the morning after an overnight fast (no food and drinks for ≥ 10 h) with a fingertip prick, at baseline, and at 3, and 9 months. The result, together with a photo of the measurement on the device, will have to be entered in the electronic questionnaire sent by email. The Contour Plus Blue glucose monitor was tested in different studies, showing compliance with the International Organization for Standardization accuracy criteria (ISO 15197:2013 [79]) and significantly lowers mean absolute relative differences from the reference value, compared to four other blood glucose monitor systems [80, 81].

HbA1c levels will be estimated using a high-performance liquid chromatography assay, at baseline, and at 3, and 9 months. Participants will collect four drops of blood from a fingertip prick in an HbA1c test tube using the materials and instructions provided. The test tubes will be sent to the Amsterdam UMC – VUmc clinical laboratory to perform the assay, using a medical return envelope, at the day of collection. When temperatures are < 4 or > 25 °C, participants will be asked to drop off the package at a parcel delivery point. This procedure was previously tested and showed feasible and reliable results, with an uncertainty of 3.7% [82].

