Nevertheless, education about timing is a low-cost and easy enhancement to the existing CLIs, as long as there is an infrastructure present to share the presentations, like the MiGuide platform. If found effective, education on timing can be seen as an addition to existing CLIs, as well as to routine care. Even null findings will provide us with valuable information, and give us the opportunity to research why effects found in highly controlled settings may not be transferable to real-life settings.

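### The adverse-event recording rule requires a sustained physical effect, so it does not fit transient hypoglycaemia, the only hazard the protocol names; an absence of recorded episodes could not be read as evidence of no harm

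*Protocol article*

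**What the plan says.** All places are in the protocol article.

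- **Adverse event reporting and harms {22}** gives the hazard and the step taken against it: "To reduce the chance of adverse events (i.e. risk of hypoglycaemia), people taking sulfonylurea medication will be excluded from participation". It says that possible events are explained in the first group session and that "participants are advised to discuss possible events with their lifestyle coach and general practitioner". The recording rule covers "Any events that are spontaneously reported by participants or observed by the investigator and that have a sustained effect on the physical wellbeing"; these events are documented and reported.
- **Eligibility criteria {10}** excludes people who "take sulfonylurea medication". The reason begins "as the effects of reducing the eating window (part of the TIMED CLI) on the risk of hypoglycaemia in participants taking sulfonylurea medication" and ends by calling those effects insufficiently known. Table 1 lists type 2 diabetes among the conditions that qualify an overweight adult for entry.
- **Relevant concomitant care {11d}**: "There are no restrictions regarding concomitant care and medication use during this study".
- **Fasting blood glucose and HbA1c**: participants use a home meter, and "they measure their blood glucose in the morning after an overnight fast", at baseline, 3 and 9 months.
- **Composition of the data monitoring committee {21a}**: there is no safety board or safety committee, because the study is considered low risk.
- **Discussion**: "If found effective, education on timing can be seen as an addition to existing CLIs, as well as to routine care".

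**The concern.** The rule and the hazard do not match. The section identifies hypoglycaemia as the event to guard against. It then sets a condition that an episode of hypoglycaemia can fail simply by resolving, even when the participant reports it at once. A rule of this kind discards information the trial has already received, which is different from leaving detail to a fuller document.

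What is at stake is how the harms data can be read. The article looks ahead to adding the timing education to existing programmes and to routine care if it proves effective. Anyone weighing that step would look for hypoglycaemia counts by arm. Under the rule as written, a low or zero count would say little about how often short-lived episodes occurred, or whether they were more frequent with the timing education.

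**Working it through.** The plan gives no event rate and no safety calculation, so there is no figure to reproduce. The check sets the sections side by side.

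**1. Is the condition joint?** Yes. Section {22} links the two parts with 'and': the event must be spontaneously reported or observed, and it must have a sustained effect on physical wellbeing. A reported episode without a sustained effect meets only the first part.

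**2. Is hypoglycaemia still possible among those enrolled?** The only glucose-lowering drugs excluded in {10} are sulfonylureas. Type 2 diabetes remains a qualifying condition, and {11d} places no restriction on medication. The TIMED arm is taught a 12-hour eating window (Intervention description {11a}). The risk is reduced but not ruled out. This is an inference from these sections; the article does not state it.

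**3. Does anything else capture short-lived episodes?**
- The advice to talk to the coach or general practitioner has no recording step attached.
- Investigator observation can add little. Sessions are online ({9}), and the article describes a researcher attending only the first group session.
- The meter readings are fasting morning values at three time points. They serve as an outcome and would not detect episodes in between.
- The questionnaires described under Outcomes {12} cover quality of life, timing of food, sleep and activity, acceptability and general background. None is said to ask about hypoglycaemia. The body of Table 2 is not available, so an item listed only there cannot be excluded.
- No safety committee reviews events.

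**4. What could a count then show?** Let n be the participants in an arm, p the unknown share with at least one transient episode, and c the share of those whose episode is recorded.

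- Expected number recorded = n × p × c.
- Probability that none is recorded = (1 − p × c)^n, ignoring clustering.

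With the planned n = 50 and the rule applied strictly to episodes without lasting effect, c = 0. The expected number is 50 × p × 0 = 0 and the probability of none is 1^50 = 1, for every value of p. If 'sustained' is applied loosely, c is above 0 but unknown, and the count still informs only the product p × c.

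**5. Could the arms still be compared?** The ratio of recorded proportions is (p₁ × c₁) / (p₀ × c₀). It equals p₁ / p₀ only if capture is the same in both arms. Participants and coaches are unblinded ({17a}), and only the TIMED arm receives the timing education, so equal spontaneous reporting cannot be assumed.

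**The case against.** The strongest case on the other side has five parts.

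- **The hazard is stated only for people who are not enrolled.** Section {10} describes the uncertainty for sulfonylurea users, and {22} mentions hypoglycaemia as the reason for excluding them. This stands as a limit: a relevant risk in the remaining participants is inferred from {10} and {11d}. The advice is also mild, a 12-hour window with breakfast always eaten, given as education.
- **No safety conclusion is planned.** This stands. A reader might infer that a finding of no harm is built into the design. The documents do not support that. There is no safety endpoint and no planned comparison of harms, the forward-looking sentence in the Discussion depends on effectiveness and claims nothing about safety, and events with a sustained effect would still be recorded.
- **'Sustained' is undefined, and the full protocol is not shown.** Recurrent episodes, or one with lasting consequences, might qualify. This rules out saying that every episode is lost. It does not remove the misfit for a single episode that resolves, and the article's rule is explicit as written.
- **The size of the loss is unknown.** This stands. A reader might be tempted to attach an assumed incidence to all 50 TIMED participants. The documents give neither an event rate nor the proportion with diabetes or on glucose-lowering drugs, so any such number would be arbitrary.
- **The study is low risk, so light monitoring is proportionate.** That is a fair reason not to solicit events intensively. It is not a reason to discard a report already received about the one named hazard.

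**Conclusion.** The point holds in a limited form. The recording rule in {22} does not fit the only hazard that the same section names, and nothing else described in the article fills the gap for transient episodes. An absence of recorded hypoglycaemia could not be taken as evidence that the timing education is harmless.

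The effect is confined to harms reporting. The BMI analysis and the other planned outcomes are untouched. No number of missed episodes can be given.

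The conclusion rests on three assumptions: that 'sustained effect' carries its ordinary meaning, that some hypoglycaemia can occur in participants not taking sulfonylureas, and that the full protocol contains no broader recording rule. If the last is wrong, the article's wording alone needs correcting.

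**What to change.** Reconcile the recording rule in {22} with the hazard it names:

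- Remove the sustained-effect condition for hypoglycaemia, so that any episode reported to the research team or to a lifestyle coach, in either arm, is documented with its date and arm.
- Report the counts by arm.
- State alongside them that capture was spontaneous and unblinded, so that they are read as reported episodes and not as incidence.

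This changes what is written down, not how any participant is managed.

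Optionally, where questionnaires or coach sessions are still to come, add one identical question on hypoglycaemia in both arms. This is harder than it looks. The trial-specific questionnaires end at 9 months, with the last collection expected in April 2026. The 24-month data, due around July 2027, come from the provider's routine evaluation, so an item there means changing that instrument. Recall from the 9-month contact would span 24 − 9 = 15 months, in unblinded arms.

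The cost of the core change is one amended sentence, a small amendment through the route in {25} and slightly more event recording. Recruitment closed in July 2025, so data for periods already past will be incomplete or limited by recall, and the report should say so.

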**Fig. 2 Fig2:**
[figure not shown]
The timed lifestyle advice on sleep, food intake, and exercise for the TIMED GLI

To minimize the risk of contamination between study arms, separate presentations and distinct sections of the MiGuide platform will be used for each intervention condition. Whether participants access the appropriate content (TIMED CLI or standard CLI platform) and receive the correct presentation will be monitored. Prior to the start of each group, the researcher will confirm the correct group allocation with the lifestyle coach. In addition, one of the researchers attends the first group session to provide additional information about the research and verifies that the participants receive the presentation corresponding to the allocated study arm. As mentioned, participants identify their individual unhealthy behaviours and pitfalls, and may therefore focus on personalized selection of behaviour(s). Although all timed recommendations are explained as equally important during the sessions, participants may prioritize certain recommendations based on their personal preferences and problems. Changes in the quantity and the timing of different lifestyle behaviours will be monitored, as described in the Outcomes section.

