### Criteria for discontinuing or modifying allocated interventions {11b}

There are no criteria of discontinuing or modifying the allocated intervention. Since the trial is pragmatic, participants receive additional education, and discuss regularly with the assigned lifestyle coach which factors they will work on. This is part of the working mechanisms of the standard CLI.

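### The adverse event rule requires a sustained physical effect, so transient hypoglycaemia, the one harm the protocol names, would go unrecorded even when reported or observed

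*Protocol article*

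**What the plan says.** Adverse event reporting and harms {22} opens with the one specific risk the article mentions: "To reduce the chance of adverse events (i.e. risk of hypoglycaemia), people taking sulfonylurea medication will be excluded from participation". Eligibility criteria {10} gives the reason, which is that too little is known about "the effects of reducing the eating window (part of the TIMED CLI) on the risk of hypoglycaemia in participants taking sulfonylurea medication". The eating-window advice belongs to the TIMED CLI alone.

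The harms section then says that possible events are explained in the first group session and that "participants are advised to discuss possible events with their lifestyle coach and general practitioner". Its rule for what enters the study record reads: "spontaneously reported by participants or observed by the investigator and that have a sustained effect on the physical wellbeing of the participant will be documented".

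On medication and treatment during follow-up, Relevant concomitant care {11d} says "There are no restrictions regarding concomitant care and medication use during this study", and Criteria for discontinuing or modifying allocated interventions {11b} says "There are no criteria of discontinuing or modifying the allocated intervention".

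**The concern.** A recording rule should be able to register the harm that the plan itself singles out. Here the named harm can be brief and fully reversible, while the rule keeps only events whose physical effect lasts. The risk is also tied to a component that differs between the randomized arms, so a comparison by arm is the natural safety question.

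Methods for additional analyses {20b} plans to ask whether participants with type 2 diabetes benefit more than those without. The Discussion foresees adding timing education to existing programmes and to routine care if it is effective. A reader weighing that benefit would want the matching information on hypoglycaemia. Under the rule as written, a low or zero count would partly reflect what was eligible for recording.

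**Working it through.** The article gives no figure to reproduce, and no arithmetic applies. The check is to read the rule as a logical condition and then see whether another section makes up for it.

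**The rule.** Let A = volunteered by the participant, B = observed by the investigator, C = sustained effect on physical wellbeing. The harms section records an event if (A or B) and C.

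| Reached the study by A or B? | Sustained effect (C)? | Recorded? |
|---|---|---|
| Yes | Yes | Yes |
| Yes | No | No |
| No | Yes | No |
| No | No | No |

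The second row is the point. An episode that has resolved and that the study already knows about is left out by condition C alone. The choice between A and B does not matter, because C applies to both.

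**Does another section close the gap?**

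- *Entry exclusion, Eligibility criteria {10}.* Excluding sulfonylurea users lowers the expected risk. It does not change which events are recorded. It is the only medication exclusion, type 2 diabetes is one of the qualifying conditions, and medication is unrestricted afterwards ({11d}).
- *Glucose readings, Fasting blood glucose and HbA1c.* Participants provide a value when "they measure their blood glucose in the morning after an overnight fast" at baseline, 3 and 9 months. These readings are a secondary outcome. Three fasting values cannot count episodes between visits, and the article does not treat a low reading as an adverse event.
- *Coach and general practitioner, {22}.* Participants are pointed to both. The article does not say how what they hear reaches the study record, and if it did, condition C would still apply.
- *Investigator observation.* Sessions are online (Study setting {9}). The text after Fig. 2 in Intervention description {11a} says that "one of the researchers attends the first group session to provide additional information about the research". The scope for direct observation is therefore limited, and again condition C would apply.
- *Oversight.* The section on the data monitoring committee {21a} states that no safety board or committee exists, so no separate body collects these events.

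No section shown restores the events that condition C removes.

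**What can still be changed.** Trial status gives recruitment as completed in July 2025, the last 9-month collection as expected in April 2026, and the 24-month MiGuide collection as complete around July 2027. A new questionnaire item would therefore miss most or all of the 3- and 9-month assessments, but could still be carried at 24 months.

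**The case against.** The strongest reply is that the documented uncertainty concerns sulfonylurea users, who are excluded, and that the article states no hypoglycaemia risk for anyone enrolled. The advice is a 12-hour window with breakfast always included, given as education and not enforced, and the study is described as low-risk. That is fair, and it limits how much weight the point can carry. It does not remove it: the harms section names hypoglycaemia as its example and then sets a rule that need not record it.

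A second reply is that the article condenses a fuller protocol, and that Table 2 is not reproduced, so a question about hypoglycaemia may exist in the case report form. This also stands. The absence of a solicited question is therefore not claimed as a defect. The point rests on the sustained-effect condition, which the article states outright.

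A reader might go further in four ways that the documents do not support:

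- *That only volunteered events count.* Investigator observation is an alternative route in the rule.
- *That the entry exclusion contradicts {11d} and {11b}.* An exclusion at entry with no later medication restriction is at most a gap. It needs clarifying, but the sections can all be true together.
- *That zero events in about 50 TIMED participants would bound the risk at 3/50 = 6%.* That denominator is the whole arm. The article does not give the share with type 2 diabetes or on glucose-lowering medication, so the relevant denominator is unknown.
- *That the trial will present the advice as safe.* No section says so. The objectives and outcomes concern metabolic health, quality of life, timing behaviour and acceptability.

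**Conclusion.** The point holds in a limited form. As written, the rule leaves out hypoglycaemic episodes without a sustained effect, including those reported to or observed by the study, so the arms cannot be compared on the one harm the protocol names. Episodes with lasting consequences that are reported or observed would be recorded, so the rule does not blank out hypoglycaemia altogether.

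The conclusion rests on two assumptions. The first is that a hypoglycaemic episode can resolve without sustained effect, which the article does not discuss. The second is that the term, which the article does not define, carries its ordinary meaning. No numerical size can be given: there is no event rate and no count of participants at risk, and the absolute number may be small. The consequence is a loss of harm information. The primary BMI comparison is unaffected.

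**What to change.** 1. In the harms section, remove the sustained-effect condition for hypoglycaemia. Document every reported or observed episode in the same way in both arms, and tabulate by arm. This can begin at once for episodes still being reported.
2. Where assessments remain open, for example the 24-month MiGuide evaluation, add one yes/no item on hypoglycaemia with identical wording in both arms. State its recall limits when reporting it.
3. If the item cannot be added, state in the results paper that transient hypoglycaemia was not systematically recorded and that no safety conclusion on it can be drawn.
4. Clarify how the sulfonylurea exclusion at entry ({10}, {22}) relates to unrestricted medication use during follow-up ({11d}). This asks only for the sponsor's intended reading to be written down. The clinical rule itself is for the sponsor to decide.

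The cost is slightly more data recording, one table and possibly a notification to the ethics committee. Episodes from the 3- and 9-month assessments already completed can be recovered only through later recall, so the table will be incomplete and should be labelled so.
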